### Analyses

#### Performance -- distance function

Our primary outcome for performance will be a measure of distance in AGREE II item and domain rating profiles of the participants versus rating profiles of experts. The distance function will be calculated as the sum of the squared deviations (SS) between expert scores and participant's scores, summed over AGREE II items (SSi) and, alternatively, domains (SSd). Such a measure offers a precise and integrated summary of similarity over the whole profile of responses, and it provides a standard quadratic weighting of errors, consistent with other widely used measures of agreement, such as weighted kappa. Since the SS is typically skewed, we will use its square root in analysis. A series of one-way ANOVA tests will then be conducted to examine differences in distance function as a function of educational intervention.

#### Performance -- pass/fail

A pass/fail algorithm has been designed and pilot tested to categorize AGREE II users as meeting minimum performance competencies with the tool. This algorithm has been pilot tested and refined and is currently used by the Capacity Enhancement Program of the Canadian Partnership Against Cancer (CPAC) to hire appraisers to participate in the evaluation of more than 800 cancer PGs using the AGREE II. The pass/fail algorithm will be used to compare competency rates across the educational intervention using X^2 ^statistics.

#### Learner's scales

A series of one-way ANOVA tests will be conducted to examine differences in participants' satisfaction, self-efficacy, cognitive effort, and time-on-task scores as a function of educational intervention.

#### Test guideline ratings -- AGREE II scores

For exploratory purposes, a series of one-way ANOVA tests will be conducted to examine differences in participants' standardized AGREE II domain scores on the test PGs as a function of educational intervention.

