#### Items

The AGREE II consists of 23 items grouped into six domains: scope and purpose, stakeholder involvement, rigour of development, clarity of presentation, applicability, and editorial independence. Items are answered using a seven-point response scale (strongly disagree-strongly agree). Standardized domain scores for PGs are calculated by summing scores across the appraisers and standardizing them as a percentage of the possible maximum score a PG can achieve per domain. This method enables the construction of a performance score profile permitting direct comparisons across the domains or items. The AGREE II concludes with two global measures answered using a seven-point scale: one targeting overall quality and the second targeting intention to use the PG.

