#### Expert norms

Expert norms will be compared to participants' AGREE II performance score profiles. Expert norms will be derived by members of the AGREE Next Steps research team who will appraise the PGs used in this study (n = 10). Mean standardized scores will be used to construct the expert performance score profiles.

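### The exploratory comparison of domain scores between arms is not referenced to the expert score of the guideline rated, so it carries chance guideline mix and has no better or worse direction by itself

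*Protocol article*

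**What the plan says.** All references are to the protocol article.

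- *Test guideline ratings -- AGREE II scores*: one-way ANOVAs, labelled as exploratory, are planned to "examine differences in participants' standardized AGREE II domain scores on the test PGs as a function of educational intervention". The sentence names no expert reference and no term for the guideline rated.
- *Items*: domain scores are obtained by summing item scores and "standardizing them as a percentage of the possible maximum score a PG can achieve per domain". They are percentages that describe a guideline.
- *Guidelines* and *Participants and procedures*: ten test guidelines were picked to vary in Rigour of Development, and each participant appraises one of them. How guidelines are distributed over the arms is not stated.
- *Expert norms*: mean standardized expert scores will be produced for the ten guidelines, and "Expert norms will be compared to participants' AGREE II performance score profiles".
- *Performance -- distance function* (primary outcome): "The distance function will be calculated as the sum of the squared deviations (SS) between expert scores and participant's scores", over items and alternatively over domains. Then: "Since the SS is typically skewed, we will use its square root in analysis".

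**The concern.** A standardized domain score is high when the rater judges the guideline to be good. Whether that judgement is right depends on the guideline, and the guideline differs from participant to participant by design. An arm mean of such scores therefore mixes two things: how the raters behave, and which guidelines they happened to receive.

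Two consequences follow for the exploratory ANOVA. Variation between guidelines enters the comparison as noise. And a difference between arms, even a clear one, does not say which arm is nearer the experts. The primary outcome does measure nearness to experts, but squaring removes the sign of each error. The two results side by side could show that the arms differ in distance and in mean rating without stating whether training made raters more lenient or more severe relative to experts. What is at stake is the interpretability of a secondary description, not the main conclusion.

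**Working it through.** **Figures in the plan.** The article attaches no number to this analysis. The group sizes used below are from *Sample Size*: 20 per group, raised to 25 for missing data. That calculation reproduces. With one-sided alpha 0.05 (assumed, since alpha is not stated), 80% power and 0.79 SD, n = 2(1.645 + 0.842)²/0.79² = 19.8, so 20 per group. Power is 80.3% by the normal formula and 79.1% by the noncentral t. Nothing below alters it.

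**Step 1: what the planned contrast contains.** For one domain, let X be a participant's standardized score, E the expert norm for the guideline that participant rated, and D = X − E. For arms A and C:

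mean D(A) − mean D(C) = [mean X(A) − mean X(C)] − [mean E(A) − mean E(C)].

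The planned ANOVA uses the first bracket only. It equals the contrast in signed error when the second bracket is zero, that is, when both arms rate guidelines with the same average expert score.

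**Step 2: size of the second bracket if guideline mix is left to chance.** With between-guideline SD s and n per arm, its standard error is s√(2/n). The article gives no s, so a range is assumed:

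| Assumed s (percentage points) | n = 20 | n = 25 |
|---|---|---|
| 10 | 3.2 | 2.8 |
| 20 | 6.3 | 5.7 |
| 30 | 9.5 | 8.5 |

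For example, 20 × √(2/25) = 5.7. As a further illustration, if raters of the same guideline had an SD of 15 and s were 20, the total SD would be √(225 + 400) = 25. The variance would be 625/225 = 2.8 times what it is without guideline differences.

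**Step 3: root-SS has no sign.** Illustrative inputs: 23 items (from *Items*), item error SD 1.2 (assumed), and a uniform bias b on the seven-point scale. Root-SS is roughly √(23 × (b² + 1.2²)), which depends on b only through b². For b = +1 or −1 this is √56.1 = 7.5; for b = 0 it is √33.1 = 5.8. Simulated means are slightly lower, because the mean of a square root lies below the root of the mean: 7.41 for both +1 and −1, and about 5.7 for no bias.

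**Step 4: domain scores carry a sign but no anchor.** In the same simulation the mean expert score is 4.0, and the mean ratings are 5.0 (b = +1) and 3.0 (b = −1). The arm contrast is 2 points, yet both arms are equally far from the experts. Only the 4.0 shows that one over-rates and the other under-rates.

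**Step 5: a limit that also applies to the remedy.** Let poor guidelines be over-rated and good ones under-rated, with bias running evenly from +1 to −1 across the quality range. The mean rating stays at 4.0 and the mean signed deviation at about 0, while root-SS rises from about 5.7 to 6.4. Neither mean detects this; root-SS does.

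**The case against.** The strongest reply is that this is an ordinary exploratory analysis and is labelled as one. It stands outside the two sections headed as performance, and the objectives define performance as distance to experts and pass/fail rate. Direction of error is not among the research questions. The squared distance was chosen deliberately: "Such a measure offers a precise and integrated summary of similarity over the whole profile of responses". Similarity to experts is the accuracy question, and root-SS answers it. All of this stands, and it makes the point a limit on interpretation rather than an error or a contradiction.

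A reader might infer that no planned analysis can show whether training corrects over-rating or under-rating. The article does not support that. By Step 1, the domain-score contrast is signed and equals the signed-error contrast when the guideline mix is the same in each arm. Expert means for the same guidelines will be available to set beside it, and the planned comparison with expert norms is not restricted to an unsigned one.

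A reader might also infer that the scores are raw or that the ANOVA is invalid. The scores are standardized percentages. If guidelines are allocated by chance, their variation also sits in the residual, so the cost is precision and not validity.

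Finally, it can be said that the choice of scale for an exploratory variable may be left to an analysis plan that is not shown. But the article does name the variable to be analysed, and a more informative one can be formed from data that the trial already collects.

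**Conclusion.** The point holds as a minor one. The exploratory ANOVA as worded compares standardized domain scores with no reference to the expert score of the guideline each participant rated. Its arm difference has no better or worse direction by itself, and root-SS does not supply one.

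If guideline mix is left to chance, it adds a standard error of about 2.8 to 8.5 percentage points to the arm difference at 25 per arm (3.2 to 9.5 at 20). This rests on an assumed between-guideline SD of 10 to 30 points and on independent chance allocation. If the mix is balanced across arms, this component vanishes and only the missing anchor remains. The bias illustrations rest on an assumed item SD of 1.2 and serve to show sign, not to predict size. The primary comparison and the sample size are unaffected.

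**What to change.** Under *Test guideline ratings -- AGREE II scores*, make the analysed variable the signed deviation: the participant's standardized domain score minus the expert norm for that guideline and domain. Compare it by arm in the same one-way ANOVAs, keep it exploratory, and report it beside root-SS.

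State how it is to be read: a positive mean is average leniency relative to experts and a negative mean is average severity. A mean of zero is absence of average bias and not agreement, because over-rating and under-rating can cancel (Step 5). It also does not show whether raters became more consistent.

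The subtraction removes the part of the between-guideline variation that the expert norms capture, whether or not guidelines are balanced over arms. The cost is one subtraction per domain and participant. No new data are needed.

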#### Guideline and AGREE II experience

For exploratory purposes, measures of PG and AGREE II Experience captured at time one will be used a covariate in the analyses proposed above.

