Diffusion of the original instrument attests to its wide coverage and acceptance but also highlights the complexity of successfully facilitating the uptake of the revised version. In conducting an analysis of the ISI Web of Science (unpublished), we found 139 citations of the original AGREE paper between its publication in 2003 and December 2008, with numbers increasing every year. Lead authors represented 23 different countries and publications appeared in 95 different peer-reviewed journals -- both specialist and generalist publications. The citations represented a wide spectrum of diseases and disciplines, including cancer, cardiology, diabetes, dentistry, psychiatry, and occupational medicine.

We anticipate the demand for the AGREE II will be as high. We are promoting the AGREE II to a broad constituency and the dissemination plan is international in focus. The target audience includes a variety of stakeholder groups (clinicians, researchers, policy makers, PG developers, system leaders) and, within groups, a range of experience with PGs and the AGREE enterprise (*i.e.*, from novice to expert). Thus, the internet is a key medium for our knowledge translation and exchange (KTE) strategy. However, dissemination alone, even with a primed and interested audience, is not sufficient to maximize the application and use of the AGREE II.

Thus, we wish to explore educational interventions and leverage technical platforms to accelerate the process. E-learning (internet-based training) provides a potentially effective, standardized, and cost-efficient model for training in the use of AGREE II. A recent meta-analysis and systematic review of 201 studies by Cook *et al. *showed large effect sizes for internet-based instruction (clinical and methodological content areas) with health-profession learners [13]. Most of the studies considered knowledge outcomes and found evidence of a substantial benefit. Those studies reporting a skills outcome, however, also found a very large effect size for e-learning interventions. The findings held true in subgroup analyses comparing different learner types, contexts, topics and outcomes. Thus, e-learning appears to be a promising, effective, practical, and efficient KTE technique to consider in our context, and we will test two interventions aimed at facilitating the application of the AGREE II.

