### Sample Size

The primary analysis involves one-way analysis of variance (ANOVA) comparisons of the AGREE II performance score profiles of the three study group participants with the performance score profiles of AGREE II experts. This will be measured by the sum of squared deviations (SS) distance function. To avoid untenable assumptions regarding the relative size of the intermediate group mean, we simplify calculations by focusing on the power for testing differences in mean SS between the passive learning condition and either of the intervention groups, which represents a strong *a priori *comparison of the least and most effective interventions. Previous research has found the effect size of e-learning in comparison to no intervention to be large ranging from 1.13 to 1.50 [16-18]. Our intent is to estimate a more conservative effect size. Thus, with 20 participants per group, a one-sided test will have at least 80% power to detect an advantage of as little as ± 0.79 standard deviations for either of the intervention groups compared to the passive learning group. To account for potential missing data, we will include up to 25 participants per group for a total of 75 participants in the study.

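### Experience with guidelines and AGREE II is collected at time one, but the primary comparison is unadjusted and the adjusted version is only exploratory; a prespecified ANCOVA would probably be more precise at almost no cost

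*Protocol article*

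**What the plan says.** The Sample Size section fixes the primary method: "The primary analysis involves one-way analysis of variance (ANOVA) comparisons of the AGREE II performance score profiles". The section on the distance function takes the square root of the sum of squared deviations from expert scores and adds: "A series of one-way ANOVA tests will then be conducted to examine differences in distance function as a function of educational intervention". Intervention is the only term in that model.

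The section Guideline and AGREE II experience then states: "For exploratory purposes, measures of PG and AGREE II Experience captured at time one will be used a covariate", and applies this to all the analyses set out before it. So an adjusted version of the primary analysis is planned, but it ranks as exploratory.

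Elsewhere the protocol treats experience as important:
- The Introduction describes a target audience with "a range of experience with PGs and the AGREE enterprise", from novices to experts, and cites evidence that the two groups may gain from different kinds of training.
- The objectives include how previous experience influences the effects.
- Participants and procedures lists recruitment sources that run from trainees to first authors of published guidelines.
- A dedicated experience scale is part of the instruments.

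Randomisation is by a computer-generated sequence. The article mentions no stratification by experience.

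**The concern.** The outcome is distance from expert ratings. Prior work with guidelines and with AGREE II is a plausible predictor of that distance, and it is measured at time one. Leaving such a measure out of the primary model has two consequences. Outcome variation that experience could explain stays in the residual, so the comparison is less precise than it could be. Any chance difference in experience between arms also passes into the headline estimate.

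There is a reporting risk as well. The trial will have two versions of its primary result. If they disagree, the possibly more precise one can be set aside as exploratory, or promoted once the data are known. Fixing the rank of the two analyses in advance removes that choice.

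**Working it through.** **Inputs.** From Sample Size: 20 evaluable participants per arm, a difference of 0.79 SD, a one-sided test, at least 80% power, and up to 25 per arm recruited. Alpha is not stated, so one-sided 0.05 is assumed. The correlation r between experience and root-SS is not in the documents, so a range of 0 to 0.5 is assumed.

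**The plan's own figure.** By the normal approximation, power = Φ(0.79 × √(20/2) − 1.645) = Φ(2.498 − 1.645) = 0.803. The stated 20 per arm therefore reproduces at one-sided 0.05. A two-sided 0.05 test would need 26 per arm, which supports the assumed alpha. With the noncentral t distribution, power is 0.795 using the three-arm residual (57 df), or 0.791 using two arms only (38 df). The unadjusted reference is thus about 79%.

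**Adjusted analysis, one covariate, three-arm model.** Three changes apply:
- The residual variance is multiplied by 1 − r².
- The residual degrees of freedom fall from 57 to 56.
- Estimating the covariate slope inflates the variance by about 1 + 1/55 = 1.018.

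The effective standardised difference is 0.79 / √((1 − r²) × 1.018), put into the noncentral t with 56 df at one-sided 0.05.

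| Assumed r | Effective difference | Power |
|---|---|---|
| 0 | 0.783 | 0.788 |
| 0.2 | 0.799 | 0.803 |
| 0.3 | 0.821 | 0.821 |
| 0.4 | 0.854 | 0.847 |
| 0.5 | 0.904 | 0.881 |
| Unadjusted | 0.790 | 0.795 |

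Setting adjusted power equal to 0.795 gives a break-even of about r = 0.14. If only the two compared arms are used, power is 0.781, 0.795, 0.813, 0.840 and 0.875 for the same values of r, against 0.791 unadjusted, and break-even is about r = 0.17.

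**Two covariates instead of one score** (two arms only). Power is 0.770 if they explain nothing, 0.803 at R² = 0.09 and 0.866 at R² = 0.25, against 0.791 unadjusted. Splitting experience into several terms uses up part of the gain.

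**Chance imbalance** (assuming randomisation is not stratified by experience). For a standardised covariate, the difference between two arm means has SD √(2/20) = 0.316. P(|difference| > 0.5) = 2 × (1 − Φ(0.5/0.316)) = 2 × (1 − Φ(1.581)) = 0.114. The probability that at least one of the three pairs differs by more than 0.5 SD comes from the range of three normal means and is about 0.25. At 25 per arm the two figures are about 0.08 and 0.18.

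An imbalance of 0.5 SD moves the unadjusted difference by r × 0.5, which is 0.15 SD at r = 0.3 and 0.25 SD at r = 0.5. The target difference is 0.79 SD.

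**The case against.** The strongest reply is that nothing in the plan is invalid. Randomisation makes the unadjusted comparison unbiased in expectation, and chance imbalance is not systematic bias. This stands.

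A reader might infer that imbalance in experience is never corrected. The text does not support that: the covariate is to be used in all the analyses set out before it, including the distance function and the learner scales. The issue is which analysis ranks as primary.

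A reader might also infer that sizeable imbalance is likely. A probability of 11% per pair, or about one in four for any pair, does not make it likely. The article's silence on stratification does not show that there is none, because a condensed article often leaves such detail to the full protocol.

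Nor can lost power be stated as a fact. It depends on a correlation that the documents do not give. There are reasons to think it could be weak: AGREE II was released only in autumn 2009 and the study hoped to finish in 2010, so experience with the tool itself may vary little. Earlier work also found no differences in rating patterns between stakeholder groups. That finding concerns stakeholder type rather than experience, but it limits what can be read from the recruitment mix.

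Finally, the protocol speaks of several experience measures on a scale still to be modified, so there is no ready-made single score. This also stands, and the fix has to supply one. Adjusting for experience as a main effect does not answer the separate question of whether experience modifies the training effect.

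**Conclusion.** The point holds as an efficiency and prespecification matter, not as an error of validity. A baseline measure that the protocol regards as relevant is kept out of the primary model, although using it there costs almost nothing.

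On the plan's one-sided test, with alpha 0.05 assumed, the gain in power over 79% is about 3 points at r = 0.3, 5 at r = 0.4 and 9 at r = 0.5. There is little or no gain at r = 0.2 or below, and a loss of about one point at r = 0. All of this is conditional on the assumed correlation. The possible loss is small and the possible gain larger, in a trial sized to just reach 80% power. That is enough to recommend the change.

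**What to change.** Before any outcome data are seen:
1. Define one summary experience score from the modified experience scale, stating which items enter and how they are combined.
2. Make the primary analysis of root-SS an ANCOVA with intervention and that score as a linear term.
3. Keep the unadjusted one-way ANOVA as a sensitivity analysis.
4. Do the same for satisfaction, self-efficacy, mental effort and time-on-task.
5. Leave the question of whether experience modifies the effects as a separate exploratory analysis.

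The change needs only wording and a scoring rule. It requires no new data, participants or procedures. Its statistical price is one degree of freedom, and about one point of power if experience turns out to be unrelated to the outcome.

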Key evidence-based principles exist that underpin the development of technical training and multimedia learning to which we will adhere. The Instructional Systems Development framework, including the ADDIE (analysis, design, development, implementation, and evaluation) model of instructional development will serve as our approach in the design and refinement stages of our intervention [14]. The work by Clark *et al. *will inform the structure and specific content types that will be incorporated [15-18]. Narration choices, contiguous labeling, and the use of graphics will follow the principles of multimedia learning [17,19]. Principles derived from cognitive load theory will also be taken into consideration in the design of the educational interventions [16,20].

In a meta-analysis and systematic review of instructional design variations in web-based learning, Cook *et al. *found that increased interactivity, practice exercises, repetition, and feedback were associated with improved learning outcomes [13]. However, while the evidence base underpinning the efficacy and design principles of internet-based training materials are well established, there remain questions regarding the optimal application of these principles for particular interventions. For example, both worked examples (demonstrations) and practice exercises with feedback have been shown to be effective training methods [17]. Yet some evidence suggests that novice learners may benefit more from worked examples, and expert learners more from practice [16,18]. Moreover, many recommended instructional design interventions such as interactivity, practice exercises, or repetition may take longer to develop, and also take up more of the learners' time, potentially leading to less efficient training. In developing an optimal on-line training intervention for the AGREE II, we also aim to study some of these key instructional design variables and time-on-task.

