Our research objectives are: to design and refine an on-line AGREE II training program comprised of a multimedia didactic overview tutorial; to design and refine an on-line, interactive AGREE II training program, comprised of the overview tutorial plus an interactive practice exercise with feedback module; to compare the two interventions against a standard control (access to static PDF version of the user's manual) and to evaluate learners' performance (distance function to experts, pass/fail rate), satisfaction, self-efficacy, mental effort, and time-on-task with the AGREE II; and to compare how previous experience with PGs and the AGREE II influence these effects.

Two core research questions are considered: Compared to the passive learning of the materials, does an on-line training program, with or without a practice exercise, improve learners' performance and increase learners' satisfaction and self-efficacy/-confidence with the AGREE II and AGREE II user's manual? Are there differences across the outcome measures between the two educational intervention groups? Are these differences influenced by learners' experiences with PGs or the AGREE II?

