### Study design

A single factorial design with three levels of educational intervention is proposed. The levels are:

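### Experience enters only as a covariate, which on the standard reading cannot show whether experience changes the training effect, a question the protocol sets itself

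*Protocol article*

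**What the plan says.** The last two paragraphs of the Introduction set out the aims. One objective is "to compare how previous experience with PGs and the AGREE II influence these effects". After asking about differences between the two intervention groups, the research questions continue: "Are these differences influenced by learners' experiences with PGs or the AGREE II". Earlier, the Introduction gives a reason for interest in this, citing some evidence that "novice learners may benefit more from worked examples, and expert learners more from practice".

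The design has one factor: "A single factorial design with three levels of educational intervention is proposed". For the primary outcome, "A series of one-way ANOVA tests will then be conducted to examine differences in distance function as a function of educational intervention". The learner scales and the standardized domain scores are handled the same way, and pass/fail rates are compared by a chi-square test.

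Experience appears in one sentence of the Analyses section, under Guideline and AGREE II experience. Labelled exploratory, it says that "measures of PG and AGREE II Experience captured at time one will be used a covariate in the analyses proposed above". The article names no interaction term, stratified analysis or subgroup contrast.

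**The concern.** The objective and the research question ask whether the difference between arms depends on prior experience. A covariate added to a one-way ANOVA answers something else. It removes the part of the outcome that experience explains and compares the arms with a common effect across experience levels. That can sharpen the comparison, but the model has no parameter for a difference in effect.

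An analyst who follows the text would report an experience-adjusted arm effect and have nothing to say on the stated question. If training helped mainly one kind of learner, the analysis would report the average and give no sign of the variation. For pass/fail there is a second difficulty, because a plain chi-square test has no place for a covariate.

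**Working it through.** **Inputs from the protocol article.** Three arms. Under Sample Size, "with 20 participants per group, a one-sided test will have at least 80% power". The difference that this power refers to is 0.79 SD, for an intervention arm against passive learning. Recruitment is up to 25 per arm.

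**Assumptions, not in the article.** Alpha 0.05; outcome SD scaled to 1; experience as a two-level variable split evenly within each arm. The experience-specific effects below are illustrative.

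**1. The plan's own figure.** Normal approximation, one-sided: 0.79 × √(20/2) = 2.498; 2.498 − 1.645 = 0.853; power = Φ(0.853) = 0.803. With the noncentral t it is 0.791. The stated 80% reproduces and is not in dispute.

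**2. What the covariate model estimates.**
- Additive model: outcome = arm + experience + error, with one arm coefficient for all participants. Under an even split that coefficient estimates the average of the two experience-specific effects, ½(effect in novices) + ½(effect in experienced users).
- Interaction model: adds arm × experience. With three arms this is 2 extra coefficients per experience measure.

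5,000 simulated trials per case, 20 per arm, with an effect in one intervention arm only:

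| Effect in novices / experienced (SD) | Average by formula | Mean additive estimate | Additive arm test rejects | 2-df interaction test rejects |
|---|---|---|---|---|
| 0.79 / 0.79 | 0.79 | 0.79 | 71% | 5% |
| 1.58 / 0 | 0.79 | 0.79 | 64% | 72% |
| 0.79 / −0.79 | 0 | 0.00 | 4% | 72% |

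The first two rows give the same additive estimate, so that estimate cannot separate a uniform effect from one confined to novices. The third row is a limiting case that shows how the model behaves. It is not a pattern the article predicts.

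**3. What the interaction model could deliver.** The pairwise interaction is a difference of two differences, so it combines four cell means. At 20 per arm each cell holds 10:
- SE = √(4 × 1/10) = 0.63 SD.
- 95% CI half-width, with 60 − 6 = 54 error degrees of freedom: about 2.0 × 0.63 ≈ 1.3 SD.
- Power for an interaction of 0.79 SD (noncentral t): 23% two-sided, 34% one-sided.
- Power for 0.82 SD (normal): 0.82/0.632 = 1.30; 1.30 − 1.96 = −0.66; Φ(−0.66) ≈ 25% two-sided.
- Interaction detectable with 80% power, two-sided: 1.80 SD.

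At 25 per arm, SE = √(4/12.5) = 0.57 SD, two-sided power at 0.79 SD is 28%, and the detectable interaction is 1.61 SD.

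**The case against.** The strongest reply is that the sentence is brief, sits in a condensed article, is labelled exploratory, and does not say that experience enters as a main effect only. The authors may have used the word covariate loosely, and exact model terms can be left to an analysis plan that is not shown. Part of this stands: the fault depends on the standard reading, and the exploratory label lowers the stakes. But the article does name a method for this question, and in ordinary usage that method does not address it. Nothing elsewhere in the article widens it.

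A second reply is that the sample is too small for an interaction to be useful. The low power is real, and it is a reason to report an estimate with its interval and no firm conclusion. It is not a reason to fit a model that cannot show the effect at all.

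Two stronger readings are tempting and should not be drawn:
- **That the Introduction predicts opposite effects in novices and experts between these arms.** It reports only some evidence, and that evidence contrasts worked examples with practice. The tutorial is described as a brief overview and nowhere as a worked example. The practice arm receives the same tutorial plus practice, so the arms are nested and no crossover between them follows.
- **That experience is measured too late because the procedures mention only post-test scales.** The analysis sentence places its capture at time one, which most naturally means baseline, so no change of timing is called for.

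**Conclusion.** The point holds: a stated objective and research question concern effect modification, and the one analysis assigned to experience, read in the standard way, contains no term for it. This mismatch of model and question does not depend on the illustrative effect sizes. The precision figures do depend on the assumed even split and two-level experience variable: a pairwise interaction SE of about 0.63 SD at 20 per arm, and roughly 23–25% two-sided power for an interaction of about 0.8 SD. An uneven split would make them worse. The corrected analysis would therefore give only an exploratory answer. The primary comparison of the distance function, and the sample size for it, are unaffected.

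**What to change.** Reword the sentence under Guideline and AGREE II experience along these lines:

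*For exploratory purposes, each experience measure and its interaction with intervention will be added to the ANOVA models. For pass/fail, a logistic model with the same terms will be used in place of the chi-square test in this analysis. The interaction and the arm differences across experience levels will be reported with 95% confidence intervals.*

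Name the experience levels or scores at which arm differences will be shown, and fix them before the data are seen. Keep the exploratory label and do not read a non-significant interaction as evidence of a uniform effect.

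The cost is a wording change and 2 degrees of freedom per experience measure for the interaction, so 4 if PG and AGREE II experience enter as two measures. Intervals will be wide, about ±1.3 SD at 20 per arm under the assumptions above. No change is needed to the design, the sample size, the data collected or the primary analysis.
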